### Data Management and Ethics

The provider of the Heart Angel platform, Virtuagym, has a data management and privacy policy that is in accordance with the General Data Protection Regulation under the law of the European Union (GDPR) and Dutch laws for data protection. Because of the sensitive nature of the patient study, several additional measures will be taken to protect patients’ privacy. These include the following: (1) private chat groups will be created to only allow each patient to communicate with his/her coach but no others in a secured environment. (2) Questionnaire data will be stored on a local server, and no names or email addresses but only participant IDs will be used to identify questionnaire data. The participant IDs will not be used for the Axivity AX3 nor for the Neo Health One devices, in order to prevent risks of data breach in cases where the devices are lost. When these devices are returned, data will be removed from the devices and saved on a secured local computer at CZE. After the study, all data on the server of Heart Angel will be deleted, including patients’ user accounts, and only anonymous and aggregated data will be archived for research purposes.

Considering the low risk of this RCT, we have been granted an exemption from insurance by the Medical Research Ethics Committees United (MEC-U) according to Article 7, paragraph 6, of the Medical Scientific Research Act with People (WMO). The study protocol (including the feasibility trial) was formally approved by the MEC-U on February 26, 2018 (NL 62142.100.17/R17.51; see Multimedia Appendices 3 and 4), and by the local ethical committee at CZE in May 2018.

## Results

### Relevant Results From the Feasibility Study

Results from the feasibility study strongly suggest that the planned RCT is feasible. First of all, from both interviews and objective data measured by the self-tracking device (see Figure 7 for all patients’ daily steps over the study week), it was evident that patients perceived the walking exercise very positively and they were able to almost always perform the exercise according to the plan. They also considered the exercise to be useful and pleasant to do, and did not experience any physical or mental problems with the exercise. A few patients even mentioned that they would like the durations of the exercise to be longer, and this proposition will be supported in the RCT with the increasing duration of the exercise over the 3 weeks.

**Figure 7 figure7:**
[figure not shown]
Number of steps walked for each patient throughout the 7-day feasibility study.

Second, during the interviews, patients indicated that they had no trouble wearing both the Axivity AX3 and the Neo Health One devices. Sensor data from both devices suggest that the compliance rates of wearing the devices were close to 100% (54/56 days [96%] from 8 patients). When the patients went to sleep, they usually put the devices near their beds so that they will not forget wearing them in the next morning. Most patients found it convenient to wear one of the devices on the wrist and the other one as a clip on their belts or trousers. This observation and the fact that Axivity AX3 as a measurement device is more valid at lower limb positions [40] informed our decisions for the devices’ wearing positions in the protocol. In addition, all patients were able to fill out the questionnaire upon receiving emails.

Finally, usage data from the Heart Angel app showed that patients and coaches (the nurse practitioners) were able to use the app for chatting. Figure 8 shows the number of messages sent to and from the patients. We did find that some patients sent the messages to the wrong places—instead of sending directly to the coaches, the messages were posted to their public profile in the app. We will take this into account and explain the messaging function more clearly to the patients in the RCT.

**Figure 8 figure8:**
[figure not shown]
Number of messages sent to and from the patients.

### Expected Results for the Main RCT

We are planning to enroll the first patients in September 2020 and the RCT is expected to be completed by the end of 2021. After the completion, statistical analyses will be conducted based on the planned method reported in this protocol to determine if the two groups differ in the primary and secondary outcomes, in addition to the psychological variables under study.

## Discussion

We designed this RCT to evaluate the potential value of digital technologies—self-tracking and mobile-based coaching—in a home-based exercise program that fills the gap between surgery discharge and conventional CR programs. If our main hypothesis is confirmed (ie, patients in the intervention group would exercise more and become physically and psychologically better prepared for the formal CR than patients in the control group at the end of the trial), the study will provide a rationale to use self-tracking and mobile-based coaching in the home-based program. The technologies are also relatively cheap as, for example, the Heart Angel platform is free for users and a self-tracking device similar to Neo Health One could cost less than €20 (approximately US $22.5). Although a cost-effectiveness analysis is beyond the scope of this protocol, the results of the trial should provide good estimates about the benefits of the technologies and insights about the required workloads from nurse practitioners. If the hypothesis is not confirmed, the results may imply that giving patients a more structured exercise program in combination with an implementation intention procedure is sufficient to support them during the gap period without technologies.

One apparent limitation of the study is that the 2 home-based CR conditions are not directly compared with the usual care. Although ideally adding such a baseline condition is useful, given practical constrains (eg, time, financial resources) our design can be justified. Both previously published research [9] and expert opinions from local physicians suggest that under the current practice, patients are clearly not supported enough and they do not exercise enough during the gap period. Thus, compared with this *straw man* condition, the condition with the low-tech exercise program is a more meaningful baseline for evaluating the technologies, because it requires minimum effort to improve the usual care. Another limitation is that our experimental design does not allow us to disentangle the beneficial effects of self-tracking and e-coaching. For example, it might be that self-tracking is the main active component of the intervention, so the costs associated with human coaching can be saved. While future research is needed to accurately separate the effects, the planned exploratory analyses on app usage data may provide preliminary answers. A third limitation relates to potential reactivity to the measurement device in the control group. Although the Axivity AX3 device does not support self-monitoring, merely wearing the device may increase patients’ awareness of their PA levels and motivate to perform more activities [56-59]. This limitation does not invalidate the testing of the differences between the trial conditions, but caution should be exercised when generalizing the results of the control group to the low-tech solution in practice. Despite the limitations, our study should provide valuable data for bridging the discharge–rehabilitation gap in the current CR practice and more generally contribute to the growing literature on enhancing traditional center-based CR with digital technologies [6,21].

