### Sample Size Calculation

We used a minimum effect size of interest approach to calculate the sample size needed to detect a statistically significant difference between the intervention group and the control group in terms of the primary outcome (average daily steps over 3 weeks). In an internal discussion between researchers, physicians, and CR experts at CZE, a 2000-step daily difference was proposed to be the minimum effect size of interest, and a 3000-step within-group standard deviation was assumed based on [32]. These assumptions amount to a moderate to strong effect size in terms of Cohen *d* of 0.67, which is justifiable given the large differences between the two conditions in terms of costs. Based on a simulation study in the R statistical programming environment [33], 100 participants (50 in each group) are required to have a 90% power to detect the effect at a significance level of .05. Because we will also have day-level data for steps over 3 weeks, multilevel regression models can also be used for examining the differences in PA between the two groups, which should have much higher power due to the large number of observations (ie, data collected over 21 days by 100 patients). Details of the simulation-based power analysis (and the R code) can be found in Multimedia Appendix 2.

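### An unconfirmed superiority hypothesis cannot support the reading that the low-tech programme is sufficient; a null result should be judged by the confidence interval against 2000 steps

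*Protocol article*

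**What the plan says.** The Discussion gives the main hypothesis in compound form: "patients in the intervention group would exercise more and become physically and psychologically better prepared for the formal CR" than patients in the control group. It then states what follows if this fails: "the results may imply that giving patients a more structured exercise program in combination with an implementation intention procedure is sufficient to support them", with no technologies needed in the gap period.

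The Sample Size Calculation section sets a different aim, namely "to detect a statistically significant difference between the intervention group and the control group in terms of the primary outcome". It declares 2000 steps a day the minimum effect of interest, assumes a within-group SD of 3000, and arrives at 50 patients per group for 90% power at the .05 level. It gives no equivalence or non-inferiority margin.

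Three other places bear on the point.
- The limitations paragraph of the Discussion concedes: "One apparent limitation of the study is that the 2 home-based CR conditions are not directly compared with the usual care". It also says of the control group: "Although the Axivity AX3 device does not support self-monitoring, merely wearing the device may increase" their awareness of how active they are, and it asks for caution in carrying control-group results over to practice.
- Primary and Secondary Outcomes does not strongly predict significant effects on the fitness measures at this sample size.
- Statistical Analysis uses the .05 level but gives more weight to estimated effect sizes when judging clinical significance.

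**The concern.** Failing to show a difference is not evidence that there is none, and still less that the comparator is good enough. The two-arm contrast can speak to what the technologies add to the walking programme. It cannot say whether the walking programme alone supports patients adequately, because nothing in the trial tests that.

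The trigger is also loose. Because the hypothesis joins steps, fitness and psychological preparation, it can go unconfirmed while the step comparison is positive. The sentence would then offer the sufficiency reading despite a demonstrated gain on the primary outcome.

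What is at stake is the conclusion after a null or mixed result. An inconclusive trial could be cited as grounds for leaving the technologies out.

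**Working it through.** **Inputs.** Difference 2000 steps/day, SD 3000, 50 per group, 90% power and α = .05, all from Sample Size Calculation. A two-sided test is assumed because sidedness is not stated. No dropout is assumed, since the article states no allowance for it.

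**1. The plan's own figure.**
- Normal approximation: n per arm = 2 × (1.960 + 1.282)² × (3000/2000)² = 47.3, so 48 per arm. A one-sided test would need only 39, so two-sided is the reading that fits.
- Exact noncentral t: 49 per arm gives power 0.904, and 50 per arm gives 0.910.
- The stated 100 patients for 90% power is reproduced.

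**2. Precision of the step difference.**
- SE = 3000 × √(2/50) = 600.
- t(0.975; 98 df) = 1.984, so the 95% half-width is 1.984 × 600 ≈ 1191 steps.

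**3. What non-significance leaves open.**
- An observed advantage below 1191 is non-significant.
- The upper limit is below 2000 only if the observed advantage is below 2000 − 1191 = 809.
- At the planned SD, the results divide as follows:

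| Observed difference (intervention − control) | Significant in favour of intervention? | 2000 excluded? |
|---|---|---|
| below about 809 | no | yes |
| about 809 to 1191 | no | no |
| above about 1191 | yes | no |

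The middle row is where the Discussion's sentence could be applied although the data still allow the effect that the trial was built to find.

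**4. How often this matters, on the protocol's own terms** (simulation, 400,000 trials, SD 3000, 50 per arm).
- True difference 2000: 9.0% of trials are non-significant. In 72% of those (0.0646/0.0896) the interval still includes 2000. The upper limit falls below 2000 in only 2.5% of trials.
- True difference 0: the upper limit falls below 2000 in 91% of trials.

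A confidence-limit rule therefore cuts the chance of wrongly dismissing a true 2000-step benefit from 9.0% to 2.5%, and it remains attainable when there is no benefit.

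**5. Sensitivity to the SD.**
- SD 3500: half-width 1389, so the unresolved zone is 2000 − 1389 = 611 to 1389.
- SD 4000: half-width 1588, zone 412 to 1588.

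Fewer analysed patients also widen the interval. Power at 2000 steps is 88% with 45 per arm and 84% with 40.

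**The case against.** The best defence is that the sentence is a hedged remark in a Discussion and not a decision rule. Statistical Analysis already ranks effect sizes above the p value. The missing usual-care arm and the possible reactivity to the accelerometer are disclosed in the next paragraph. Read generously, sufficiency means only that nothing worthwhile is gained by adding the technologies, which the trial does compare. All this is fair, and it keeps the point to one of wording. It does not remove it: the sentence is not limited by those disclosures, and no section says what a null result must look like before even the generous reading is allowed.

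Three stronger readings may tempt a reader, and the document does not support them.
- *That the cost argument contradicts itself.* Sample Size Calculation calls the effect size one "which is justifiable given the large differences between the two conditions in terms of costs", while the Discussion says "The technologies are also relatively cheap as, for example, the Heart Angel platform is free for users". The first compares whole conditions, and the intervention includes monitoring and coaching by nurse practitioners. The second prices only the platform and the wristband. The Introduction and the Discussion both treat staff workload as a separate cost, so the statements are compatible.
- *That the trial is underpowered for smaller gains, such as 1000 or 1500 steps.* The protocol declares 2000 the minimum of interest after discussion among researchers, physicians and rehabilitation experts. Nothing in it makes a smaller gain the target, and low power below a declared minimum is inherent in any such calculation.
- *That 2000 steps is implausibly large against the prescribed walking.* This needs an assumed cadence and counts only the two daily sessions. The programme also sets an overall daily activity goal, and the outcome is total daily steps.

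**Conclusion.** The point holds as a minor fault of interpretation. An unconfirmed hypothesis in this superiority design cannot support sufficiency of the low-tech programme. At the planned SD, non-significance alone does not exclude the protocol's own 2000-step effect when the observed advantage lies between about 809 and 1191 steps. A null result whose upper limit is below 2000 would support a narrower statement: no added step benefit of the size of interest.

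The figures assume a two-sided 95% interval, SD 3000 and all 100 patients analysed. A larger SD or any loss of patients widens the unresolved zone. A reader might infer that the design or sample size is at fault; neither is, and the primary analysis need not change.

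**What to change.** Replace the Discussion sentence on an unconfirmed hypothesis with wording such as:

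> *If the upper 95% confidence limit for the difference in average daily steps is below 2000, we will conclude that the technologies add no step benefit of the size of interest over the low-tech programme; otherwise a non-significant result is inconclusive.*

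Drop the word *sufficient*. This ties the conclusion to the primary outcome alone, so a missed fitness or psychological effect no longer triggers it, and it suits the emphasis on effect sizes in Statistical Analysis.

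The cost is text only, with no change to design, sample size, outcomes or analysis. The downside is a weaker claim after a null result, and some null results will have to be reported as inconclusive. The wording should be settled before outcome data are seen.

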## Appendix

Multimedia Appendix 1 CONSORT-EHEALTH checklist.

Multimedia Appendix 2 Self-report measures.

Multimedia Appendix 3 Initial review and comments by MEC-U.

Multimedia Appendix 4 Second review and acceptance by MEC-U.

## Abbreviations

CR: cardiac rehabilitation
CZE: Catharina Ziekenhuis Eindhoven
GDPR: General Data Protection Regulation under the law of the European Union
HR_max_: maximum heart rate
ICT: information and communication technology
MEC-U: Medical Research Ethics Committees United
PA: physical activity
Peak VO_2_: peak oxygen uptake
RCT: randomized controlled trial
